### Process evaluation

#### Quantitative component of the process evaluation

Quantitative questionnaires will be analyzed using descriptive analyses following scaling and observed data distribution. Thus, means and standard deviations will be given for normally distributed data and medians and interquartile ranges for non-normally distributed data. Categorical data will be reported by absolute and percentage frequencies. Descriptively, different professions and the different study centers will be compared.

#### Qualitative component of the process evaluation

All qualitative data will be transcribed, pseudonymized, and analyzed using qualitative content analysis according to Kuckartz (18), adhering to established methodological standards and quality criteria. Initially, a coding frame will be developed based on the sighting of 2–3 transcripts. From this, a codebook will be developed that will be applied to code the remaining transcript. All transcripts will be independently analyzed by two experienced qualitative researchers. Any disagreement in the resulting coding will be discussed, and the extent to which the independent coders agreed or disagreed will be reported descriptively (19).

The resulting category system will provide additional information to the questionnaire data and help to better understand the perspectives of patients and care providers in the field of personalized medicine.

In addition to the primary outcome, we anticipate several important findings related to the secondary endpoints across micro-, meso-, and macro-levels of the healthcare system. At the micro-level, we expect that patients will perceive benefits from the standardization of PM within the ZPMs, particularly through more consistent and equitable access to individualized therapy options. These benefits will be evaluated using a range of patient-centered outcomes, as outlined in Table 2. At the meso-level, we aim to assess the transferability of the ZPM specialist concept developed in BW to other participating sites. We anticipate identifying key facilitators and barriers to successful implementation, as well as necessary modifications to support context-specific adaptation.

Finally, at the macro-level, we expect that improved communication and collaboration among ZPMs within the national network will generate added value by enhancing patient care delivery. This may include greater harmonization of clinical structures and workflows, improved interoperability of data systems, and coordinated decision-making and resource sharing. These anticipated findings will inform future strategies for scaling and sustaining harmonized PM practices across healthcare institutions.

### Health economic evaluation

In the health economic analysis, treatment costs and intervention costs will be compared with quality-adjusted life years (QALYs) in a cost–utility analysis for both the intervention and control groups and summarized as an incremental cost-effectiveness ratio (ICER). The ICER reflects the relationship between the additional costs incurred through the ZPM (intervention) and the demonstrated benefit in terms of QALYs.

Quality of life will be assessed using the standardized EQ-5D-5L questionnaire at the start of therapy (T2; baseline), at 6 weeks (T3), and at 6 months (T4) after therapy initiation. These data will be translated into quality-adjusted life years. As cost parameters, the analysis will consider all implementation costs related to establishing the ZPMs at the intervention sites, as well as all treatment-related costs associated with PM in both the intervention and control groups. For this purpose, data will be collected from the controlling units of participating institutions that deliver PM, which provide patient-level information on cost coverage by statutory health insurance (SHI).

Since only a portion of patients are treated directly at the respective centers (in some ZPMs, <50%), and because outpatient costs are not centrally documented within hospital controlling systems—making comprehensive cost capture difficult—additional patient-level data will be collected through the following methods:

Patient self-reports on healthcare utilization will be collected based on an adapted version of the FIMA questionnaire, administered at 3 and 6 months after therapy initiation. Costs of implemented MTB recommendations (primary endpoint, Level 3) will be calculated based on the reported pharmaceuticals and therapy modalities (e.g., using data from the Lauer-Taxe drug price database). To account for process and structural costs associated with care delivery in the ZPMs, focus groups with participating centers will be conducted at the beginning of the project. These will identify both the additional costs incurred through the transition to ZPM-based care and the potential cost savings expected as a result of the structural change.

The analysis will be conducted from the perspective of SHI. The findings will be evaluated for their transferability to the broader SHI-insured population. Statistical uncertainty around the ICER will be illustrated and estimated using cost-effectiveness acceptability curves (CEACs).

At the macro-level, we anticipate that increased communication and coordination between the individual ZPMs will lead to measurable improvements in the efficiency of patient care across the network. These improvements are expected to manifest as cost savings through greater harmonization of clinical structures and processes and enhanced interoperability of data systems. Through the health economic evaluation, we aim to quantify these effects by comparing implementation and treatment-related costs between intervention and control settings, while also capturing structural and process-related cost changes associated with the network-wide adoption of personalized medicine. We expect that the findings will demonstrate that a well-connected ZPM network not only improves care delivery but also supports more efficient resource utilization, with potential implications for cost-effectiveness at the system level.

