### Trial design

The current study employs a Hybrid Type 3 design, evaluating the overall implementation while monitoring and collecting data on the clinical intervention's effects on important outcomes (9). Using a mixed-methods approach, the study integrates quantitative measurements and qualitative data collection across multiple stakeholder groups, including patients and healthcare staff. In addition, key structural and process parameters will be documented over time, and a health economic evaluation will be conducted. The study design is based on a modified stepped-wedge approach: The participating centers transition at different time points from a control condition—characterized by site-specific, non-harmonized PM practices—to the intervention condition, which reflects harmonized PM procedures. While this approach resembles the classical stepped-wedge design in its sequential rollout across sites, it deviates in one important aspect: The timing of the transition is not randomized. Instead, it is determined by administrative and organizational readiness. Specifically, a center enters the intervention group on the date documented in its certification form, which confirms that essential steps toward PM harmonization have been implemented. The certification criteria align with the standards set by the German Cancer Society (Deutsche Krebsgesellschaft) (8).

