### Sample size

The study aims to recruit a total of 4,807 patients, including 3,507 in the intervention group and 1,300 in the control group. The following assumptions underlie the sample size estimation: For nine newly established ZPMs (centers), two centers would be acceptable as dropouts. At least four existing centers in BW are considered unlikely to drop out, and seven newly initiated ZPMs serve as the basis for the sample size estimation. The new centers will contribute to controlling/intervening patients before/after initiation as ZPM, while the existing ZPM will only have intervention patients. This approach, inspired by the stepped-wedge design, has already been successfully used in several projects funded by the Innovation Fund (10). An average stay of 6 months in the control phase is assumed. It is estimated that each comprehensive cancer center (CCC) will have between 300 and 500 patients with PM, resulting conservatively in 1,300 control patients. This is compared with an estimated 3,500 ZPM patients from existing ZPM and those newly implemented during the study period. With these numbers, ignoring the cluster effect, differences of approximately 5% can be detected in the chi-squared test (Type I error 5% two-sided) with a power of >80% (exactly 86%) and differences of 7% with >90% (exactly 96%) power. Assuming a variance inflation due to cluster effects of 2, differences of 7% can still be detected with 85% power, and with very high cluster effects of 4 or 6, differences of 10% or 13% can be detected with 85% power.

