### Participant timeline

Table 3 shows the participant schedule throughout the intervention period.

**Table 3 T3:** Participant schedule.

Specification of data collected	Participant schedule			
	Enrolment	2–3 months post-enrolment	5–6 months post-enrolment	Close-out
Time point/assessment	T0	T1	T2	T3
Study participation				
Eligibility screen	X			
Informed consent	X			
Allocation	X			
Clinical data collection				
Socio demographics	X			
Diagnose	X	X	X	
(Further) therapies in the last 3 months outside the MTB recommendation	X	X	X	
MTB recommendations		X	X	
Follow-up on MTB recommendations		X	X	
Scheduled end (follow-up completed after 5–6 months)				X
Reason for premature end				X
Patient questionnaire				
Socio demographics	X	X	X	
Living situation	X	X	X	
Financial Situation	X	X	X	
Social support	X	X	X	
EQ-5D-5L (health-related quality of life)	X	X	X	
EORTC QLQ-C30 (disease-related quality of life)	X	X	X	
FIMA (Utilization of health services)	X	X	X	
Patient satisfaction	X	X	X	
Patient interviews				
Understanding, expectations, and attitudes toward PM, perceived care		X	X	

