#### Health economic evaluation

For the purpose of the health economic evaluation, health-related quality of life, mortality, and cost data have to be collected for intervention and control patients. Quality of life is assessed based on patients' responses to the validated EQ-5D-5L questionnaire at study enrollment, 2–3 months after enrollment, and 5–6 months after enrolment (14, 15). Deaths are recorded in the questionnaire filled out by site staff. Inpatient treatment costs incurred at the university hospitals are extracted from the respective controlling departments. If the cancer treatment of patients does not take place at the study center itself, costs are approximated by the type of therapy recorded in the study documentation and the respective averages based on the then available controlling data from other patients. To capture other healthcare costs incurred outside the included university hospitals, an adjusted version of the FIMA questionnaire (questionnaire on the use of medical and non-medical health and care services in later life), a validated survey instrument for healthcare utilization for the German context (16, 17), is administered to patients at study enrollment, 2–3 months after enrollment, and 5–6 months after enrollment. Costs of the DNPM intervention itself are approximated through assessments made by coordinators of the study centers (a) in a quantitative survey (as part of the process evaluation questionnaire) and (b) in a focus group with the cost items of the DNPM project's overall budget as a starting point.

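### The cost-utility analysis names no adjustment for baseline utility or prior resource use between non-randomised groups, and its baseline timing contradicts the data collection sections

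*Protocol article*

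**What the plan says.** In the protocol article, under Analysis and anticipated results, the Health economic evaluation states that "treatment costs and intervention costs will be compared with quality-adjusted life years (QALYs) in a cost–utility analysis for both the intervention and control groups". The result is an ICER, with uncertainty shown by acceptability curves. No estimator, model or covariate is named.

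The groups are not formed by chance. Trial design says: "The timing of the transition is not randomized. Instead, it is determined by administrative and organizational readiness". Under Sample size, new centres supply control and then intervention patients, "while the existing ZPM will only have intervention patients".

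Baseline measures are scheduled. Table 3 (Participant timeline) marks "EQ-5D-5L (health-related quality of life) X X X", the first mark being enrolment, and marks FIMA in the same way. Under Data collection and management, the Health economic evaluation says that FIMA "is administered to patients at study enrollment, 2–3 months after enrollment, and 5–6 months after enrollment", and gives the same three times for EQ-5D-5L. The analysis section differs. It puts the EQ-5D-5L baseline at start of therapy (T2), with follow-up at 6 weeks and 6 months, and says that FIMA is "administered at 3 and 6 months after therapy initiation".

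**The concern.** A QALY over a short horizon is the area under the utility curve, and the baseline utility is one end of that curve. If the groups differ in health at entry, the raw QALY difference contains that gap even when the intervention does nothing. Costs behave similarly when prior use predicts later use. Here the groups differ by centre and by calendar time, so balance at entry cannot be assumed. The acceptability curve describes sampling uncertainty around whatever increment it is given, so a shifted increment appears as greater or lesser confidence and not as bias.

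The timing conflict decides whether the problem can be corrected. A covariate is safe to adjust for if it was measured before exposure. A start-of-therapy value comes after the tumour board decision that the intervention is meant to change, so adjusting for it could remove part of the effect.

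**Working it through.** The document gives no figure for QALYs, costs, utility SD or baseline differences, so there is nothing of its own to reproduce. What follows is a check of the schedule and then an illustration on stated assumptions.

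**1. The schedules side by side**

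| Section | EQ-5D-5L | FIMA |
|---|---|---|
| Participant timeline, Table 3 | enrolment, 2–3 and 5–6 months | enrolment, 2–3 and 5–6 months |
| Data collection, Health economic evaluation | enrolment, 2–3 and 5–6 months | enrolment, 2–3 and 5–6 months |
| Data collection, Quantitative share of the process evaluation | start of therapy (T2), 3 and 6 months | not given |
| Analysis, Health economic evaluation | start of therapy (T2), 6 weeks and 6 months | 3 and 6 months after therapy start |

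The labels also clash. In Table 2, T2 is the day of the first therapeutic intervention, after T1, the therapy decision. In Table 3, T2 is 5–6 months after enrolment.

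**2. QALY weights.** Assume visits at 0, 2.5 and 5.5 months (within the enrolment-based windows), the trapezoidal rule and no deaths:
- baseline: (2.5/2)/12 = 0.104 years
- first follow-up: (5.5/2)/12 = 0.229 years
- second follow-up: (3.0/2)/12 = 0.125 years

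**3. Spurious QALY difference.** Let d be the baseline gap and r the fraction that persists at both follow-ups. With no intervention effect the difference is d × [0.104 + r × (0.229 + 0.125)]. For an assumed d = 0.05:
- r = 0: 0.005
- r = 0.5: 0.0052 + 0.5 × 0.05 × 0.354 = 0.014
- r = 0.7: 0.018
- r = 1: 0.023

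A true gain of 0.05 at both follow-ups is worth 0.05 × 0.354 = 0.018 QALY, so the spurious difference can be as large as a real one. On the analysis section's grid (0, 6 weeks, 6 months) the range is 0.003 to 0.025.

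**4. Size against sampling error.** The group sizes come from Sample size: "The study aims to recruit a total of 4,807 patients, including 3,507 in the intervention group and 1,300 in the control group". Assume utility SD 0.25, correlation 0.5 between visits and every patient contributing. The variance factor is 0.5 × 0.0790 + 0.5 × 0.2101 = 0.1445, where 0.0790 is the sum of squared weights and 0.2101 the square of their sum. The QALY SD is 0.25 × √0.1445 = 0.095. With variance inflation 2, one of the article's own scenarios, SE = 0.095 × √(1/3507 + 1/1300) × √2 = 0.0044. A spurious 0.014 is then 3.2 SE. At inflation 6, also an article scenario, it is 1.9 SE.

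**5. Simulation with no true effect** (500 runs, 1,300 against 3,507, baseline SD 0.22, slope 0.7, no clustering):

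| Assumed gap | Unadjusted QALY difference | Adjusted for baseline |
|---|---|---|
| 0.02 | 0.007 | 0.000 |
| 0.05 | 0.017 | 0.000 |
| 0.10 | 0.035 | 0.000 |

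The SE is about 0.0028 unadjusted and 0.0014 adjusted. For the 0.02 gap the unadjusted z is 2.5, which puts the probability of a QALY gain at about 0.99 with no effect present. Clustering tempers this. At inflation 2, z = 2.54/√2 = 1.8 (about 0.96). At inflation 6, z = 2.54/√6 = 1.04 (about 0.85). The adjusted mean is zero because the simulated gap acts only through baseline utility; centre or period effects would not vanish in this way.

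**The case against.** The strongest reply is that the article is silent and does not choose a raw comparison. It is a condensed account, and the covariates of a secondary economic model may stand in a full protocol or analysis plan that is not shown. This stands as far as it goes: a reader might infer that the analysis will be run unadjusted, and the text does not say so.

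It does not dispose of the point. The article gives this level of detail elsewhere: the GEE structure, exclusion windows before certification, adjustment factors and 500 imputations with named predictors. For health economics it states what is inherited, namely the subgroups and the handling of non-adherence and missing data. The inherited non-adherence approach uses covariates in regression models, and Table 2 lists QALYs and ICER at the micro-level under the quantitative evaluation, so a regression may well be intended. But the only adjustment factors named are rare tumour and urban/rural, in secondary analyses. Neither is baseline utility nor prior use. The timing conflict is visible whatever another document says.

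A reader might also infer that a baseline FIMA is certainly held and ignored. That holds under Table 3 and the data collection section but not under the analysis section, so the sections must be reconciled first.

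The objection to the magnitudes stands. All inputs are assumed. Deaths are to be expected in advanced cancer, the Discussion anticipates attrition in self-reports, and a gap between groups need not fade at the within-patient rate. Fewer completers would lower the ratio to the SE. It is also fair that the ICER is a secondary endpoint, that non-randomisation is acknowledged, and that baseline adjustment leaves centre and calendar-time confounding in place.

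**Conclusion.** The concern holds in this form: the article compares QALYs and costs between non-randomised groups, specifies no adjustment for baseline utility or prior resource use, and contradicts itself on when the baseline is measured. It should be corrected before analysis.

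That an unadjusted QALY difference contains the baseline gap is arithmetic. The size is illustrative: about 0.005 to 0.023 QALY for an assumed 0.05 gap over 5.5 months, from no persistence to full persistence, with no deaths. The document supports no statement about how large the real gap is or which group it favours, so it cannot be said that the ICER will be biased by a given amount or in a given direction. Nor can a gain in power be claimed, because the article states no QALY test and no power target for one.

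**What to change.** 1. Reconcile the assessment times and T-labels across Table 2, Table 3, the data collection sections and the analysis section. Recruitment ended on 30 September 2024, so this means stating what was actually collected. If enrolment values exist, the analysis section should list them, including the enrolment FIMA.
2. State that incremental QALYs are estimated by regression on study arm and enrolment EQ-5D-5L utility, not the start-of-therapy value.
3. State that incremental costs are estimated by regression on study arm and the enrolment FIMA utilisation cost.
4. Include rare tumour and urban/rural in both models. Base the ICER and acceptability curves on the adjusted increments, and keep the unadjusted comparison as a sensitivity analysis.
5. State that centre and calendar-time confounding may remain after this adjustment.

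If a full analysis plan already specifies this, a reference to it and the corrected schedule are enough.

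The cost is wording and a little programming. If the enrolment schedule was followed, no new data are needed. The small downside is that missing enrolment questionnaires need imputed values, which the multiple imputation already planned and carried over to the health economic evaluation can supply.

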		Patient satisfaction and quality of life of patients treated in the MTB • Satisfaction • Quality of life	At study enrollment, 2–3 months after enrollment, and 5–6 months after enrollment	• Modified questionnaire instrument based on the PSCC-G instrument • Established questionnaire instruments for disease-specific quality of life, EQ-5D-5L, and EORTC QLQ-C30 *(included in the patient questionnaire)*
		Health economics • QALYs • Total costs (healthcare costs, intervention costs) • ICER	5–6 months after enrollment	• EQ-5D-5L • Modified FIMA questionnaire • Controlling the data of participating university hospitals • Survey of centers *(included in patient questionnaire)*
	Qualitative evaluation	Patient-level survey: • Understanding and attitude toward personalized medicine • Qualitative assessment of the implementation processes • Expectations regarding care provided by the personalized medicine services (ZPMs)/the decentralized personalized medicine (DNPM) • Perceived care before and during treatment with ZPMs/DNPM • Costs incurred in the context of personalized medicine care	At a later stage in the project	Semi-structured interviews with patients
Meso-level and macro-level	Process evaluation (quantitative)	Perspective of staff from centers for personalized medicine (ZPMs): • Degree of standardization of processes • Establishment of new coordination processes at the medical or professional level (e.g., expert committees) • Implementation and structural costs (costs incurred from transitioning to ZPM/DNPM) • Process costs (ongoing costs before ZPM, or of the individual ZPMs) • Exchange/knowledge transfer between ZPM • Exchange of harmonized data • Presence of interconnected data structures (e.g., completeness, quality) • Exchange of harmonized data between the ZPMs • Communication and decision-making structures and processes	• T0: at the time of certification • T1: at an intermediate stage in the project • T2: at a later stage in the project	Quantitative questionnaire based on the certification forms at the center, participation in meetings of the MTB working group, and analysis of the working group’s meeting minutes *(organizational structure and process survey)*

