### Data collection and management

#### Quantitative evaluation

The primary endpoint contains three tiers. At Tier 1, the primary endpoint is the number of patients who receive an indication-driven, standardized access to the new form of care—personalized diagnostics and therapy—defined as access to the MTB. For this endpoint, a standardized data collection instrument will be developed to document both the original procedure and the newly implemented one, including the extent of the changes made (e.g., additional molecular diagnostics and therapy). The new procedure will be based on predefined, evidence-based criteria established by the ZPM network in BW. At Tier 2, it will be assessed for which patients the diagnostic process or diagnostic interpretation was significantly changed. Among this group, Tier 3 evaluates the proportion of patients for whom the changes ultimately led to treatment within the framework of personalized medicine. These changes may also include recommendations for genetic counseling, which—although not directly involving therapy or additional diagnostics—represent a modification in patient care.

Secondary clinical endpoints will be assessed continuously during the study: Adverse events (AEs) and serious adverse events (SAEs) will be recorded as they occur, and overall survival (OS) and progression-free survival (PFS) will be recorded every 6 months (T4–T8) until the end of the observation period, with a minimum follow-up of 6 months and an average follow-up of 12 months.

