##### Quantitative share of the process evaluation

Organizational structure and process survey: The qualitative analysis will be supplemented by a self-report questionnaire in accordance with the certification requirements of the German Cancer Society (Deutsche Krebsgesellschaft) (8). To assess the level of establishment of the individual ZPMs, the achievement of goals during the implementation of functional areas and their integration into the ZPM will be measured. This includes an established telemedicine access for external practitioners, quality-assured molecular diagnostics, and evidence-based therapy recommendations in interdisciplinary molecular tumor boards (MTBs).

In addition, a range of patient-reported outcomes (PROs) will be assessed. These include generic quality of life, measured using the standardized EQ-5D-5L questionnaire, and disease-specific quality of life, assessed with the EORTC QLQ-C30. An additional secondary PRO is treatment-related patient satisfaction, evaluated using the Patient Satisfaction with Cancer-related Care questionnaire (PSCC-G), which has been validated in German (13). All PROs will be collected at three individual time points: at the start of therapy (T2, baseline for secondary endpoints), after 3 months (T3), and after 6 months (T4).

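### EQ-5D-5L has three incompatible schedules on two time origins, and the one named for the QALYs starts at therapy, which not every enrolled patient need reach

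*Protocol article*

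**What the plan says.** EQ-5D-5L is scheduled in five places in the protocol article, in three different ways.

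- **From enrolment.** Table 2 (Outcomes) has satisfaction and quality of life "At study enrollment, 2–3 months after enrollment, and 5–6 months after enrollment". Table 3 (Participant timeline) marks EQ-5D-5L, QLQ-C30, FIMA and satisfaction at the same three visits. The Health economic evaluation section under data collection agrees: "EQ-5D-5L questionnaire at study enrollment, 2–3 months after enrollment, and 5–6 months after enrolment".
- **From therapy start, with 3 and 6 months.** The section on the quantitative share of the process evaluation puts all patient-reported outcomes "at the start of therapy (T2, baseline for secondary endpoints), after 3 months (T3), and after 6 months (T4".
- **From therapy start, with 6 weeks and 6 months.** The Health economic evaluation section under Analysis and anticipated results uses "at the start of therapy (T2; baseline), at 6 weeks (T3), and at 6 months (T4) after therapy initiation" and says that these values are converted into QALYs.

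FIMA has three administrations from enrolment in Table 3 and in the data collection section. In the analysis section it is "administered at 3 and 6 months after therapy initiation", with no baseline.

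On length of follow-up, Table 3 has a row under clinical data collection that begins "Scheduled end (follow-up completed after 5–6 months". The Quantitative evaluation section under data collection follows OS and PFS every 6 months, "with a minimum follow-up of 6 months and an average follow-up of 12 months".

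**The concern.** The schedules cannot all hold, and the choice between them is more than a matter of labels. Enrolment is an origin that every patient has. Therapy start comes later, and some patients may never reach it. A patient who dies before therapy, or is never treated, has no therapy-start visit and so no QALY baseline under the analysis section.

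Tier 3 of the primary endpoint is the actual implementation of changed diagnostics or therapy, and the plan expects the intervention to raise it. An origin that overlaps with Tier 3 may therefore select patients differently in the two groups. The ICER would compare treated subsets, whereas the data collection section asks for quality of life, mortality and costs for intervention and control patients without restriction.

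A second risk is computational. If values collected at the Table 3 visits are placed on the time grid of the analysis section, the area under the curve is wrong even for patients with complete data.

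**Working it through.** **Step 1: set the schedules side by side.**

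| Place in the article | Origin | EQ-5D-5L | FIMA |
|---|---|---|---|
| Table 2 | enrolment | 0, 2–3, 5–6 months | no separate schedule |
| Table 3 | enrolment | 0, 2–3, 5–6 months | 0, 2–3, 5–6 months |
| Data collection, health economics | enrolment | 0, 2–3, 5–6 months | 0, 2–3, 5–6 months |
| Data collection, process evaluation | therapy start | 0, 3, 6 months | not given |
| Analysis, health economics | therapy start | 0, 6 weeks, 6 months | 3, 6 months |

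This makes two origins and three EQ-5D-5L schedules. QLQ-C30 and satisfaction have two schedules (Tables 2 and 3 against the process evaluation section), and FIMA has two. Within the analysis section the middle EQ-5D-5L is at 6 weeks and the first FIMA at 3 months, although Table 3 puts both in one patient questionnaire at the same visits.

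**Step 2: compare the labels.** T2 is the first therapeutic intervention in Table 2 (primary endpoint), 5–6 months after enrolment in Table 3, and the therapy-start baseline in the two therapy-based texts. T3 is close-out in Table 3, 3 months in the process evaluation section and 6 weeks in the analysis section. T4 is used in the text but is not a column of Table 3.

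**Step 3: size of the selection.** The article gives no share of patients who never start therapy, so the share is an assumption shown as a range. Patients without a therapy-start baseline = share × 4,807:

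- 30%: 0.30 × 4,807 ≈ 1,442
- 50%: 0.50 × 4,807 ≈ 2,404
- 70%: 0.70 × 4,807 ≈ 3,365

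**Step 4: effect of the time grid.** The article states no QALY figure to reproduce. The illustration uses the trapezoidal area in years, [(u0+u1)/2 × (t1−t0) + (u1+u2)/2 × (t2−t1)]/12, with assumed utilities 0.70, 0.60 and 0.50. The horizon is held at 6 months, so that the comparison does not mix grid and duration. Six weeks is taken as 1.5 months.

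- Grid 0/3/6: (0.65 × 3 + 0.55 × 3)/12 = 3.60/12 = 0.300
- Grid 0/1.5/6: (0.65 × 1.5 + 0.55 × 4.5)/12 = 3.45/12 = 0.2875, or 0.288
- Difference: −0.0125/0.300 = −4.2%

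The sign depends on the course of the utilities. With 0.60, 0.70 and 0.70 the results are (0.65 × 3 + 0.70 × 3)/12 = 0.3375 and (0.65 × 1.5 + 0.70 × 4.5)/12 = 0.344, about +2%.

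The cause is the weights. The middle visit counts 3 months on both grids. The last visit counts (6−3)/2 = 1.5 months on the first and (6−1.5)/2 = 2.25 months on the second, and the baseline falls from 1.5 to 0.75 months.

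The calculation places the same values on two grids. It shows what a mismatch between visits and nominal times would do, not what patients would report at 6 weeks.

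**The case against.** The strongest reply is that Table 2, Table 3 and the data collection section agree on enrolment. If data were collected that way, every patient is due a baseline, and the therapy-start texts are merely out of step. The 3 and 6 months also match the upper ends of the enrolment windows, so the 6 weeks is the only outlying interval. This is fair, and it is why the repair is small. It does not remove the contradiction, because the deviating text is the one that says how QALYs are formed.

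Three stronger readings are tempting, and the documents do not support them.

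- **That the plan excludes untreated patients or early deaths.** No sentence says so. It follows only from a literal reading of the analysis section. The data collection section names mortality as an input, has site staff record deaths, and covers all intervention and control patients.
- **That therapy start is the same as Tier 3.** The therapy-start texts do not say that the therapy must be the one the tumor board changed. Tier 3 also counts diagnostic changes and can include genetic counseling. The two overlap; they are not equal. If any therapy counts as a start, fewer patients are affected.
- **That follow-up for OS and PFS is cut to 5–6 months.** Table 2 makes the clinical endpoints event-driven, and the data collection section continues OS and PFS every 6 months. Recruitment ended on 30 September 2024 and data collection runs to the end of November 2025, 14 months later. The Table 3 row needs clarifying, but the article as a whole does not plan that loss.

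Multiple imputation, which the plan extends to the health economic evaluation, does not settle the matter. A therapy start that never happens is an undefined origin, not a missing value.

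**Conclusion.** The point holds as an internal inconsistency that should be fixed. EQ-5D-5L has three schedules on two origins, QLQ-C30, satisfaction and FIMA have two schedules each, and T2 and T3 carry several meanings. If the analysis section were followed literally, the ICER would be undefined for patients without a therapy start, or conditioned on an event after enrolment that may differ between groups.

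The number affected cannot be derived from the article; the range in the working rests on the assumed share. The grid effect of about 4% rests on assumed utilities and can change sign. Neither figure is an estimate of bias in this trial.

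The primary endpoint, its GEE analysis and the sample size are untouched. The outcomes concerned are secondary or health economic, and the plan does not interpret secondary p-values confirmatively. With recruitment complete, the origin should be settled before analysis so that it cannot be chosen after seeing results.

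**What to change.** 1. Define the QALY, cost and patient-reported outcome analyses from enrolment for all enrolled patients, as both tables and the health economic data collection section already have it.
2. Use actual assessment dates and recorded death dates in the area under the curve, in place of nominal months.
3. Confirm that data were collected as in Table 3, then align the process evaluation section and the health economic analysis section, including the FIMA times. If collection differed, state the schedule actually used and a rule for patients without a therapy start.
4. Use one set of T labels throughout.
5. In Table 3, state that the scheduled end at 5–6 months does not end OS and PFS follow-up, and show that follow-up separately.

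The cost is wording and the use of dates in the analysis. If the data follow Table 3, nothing further needs to be collected for the questionnaires.
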